#### Recruitment

The random method will be used for sampling. First, four comprehensive health centers will be randomly selected in Bandar Abbas, from which, two will be randomly assigned to the intervention group and two to the control group. The number of samples from each center will be determined according to the population covered by the center. To select eligible individuals, SD will randomly select a family record belonging to the population covered by the selected comprehensive health centers.

Then, to select other people, the researcher will visit all houses on the right side of the first selected record. After identifying the samples and obtaining informed consent from them, the phone number of all samples will be obtained for correspondence.

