#### Inclusion criteria

Smoking hookah for 4 times a week in a duration of at least 6 months before the data collection [27, 28], being fluent in native language, having no history of psychiatric disorder, cardiovascular disease (acute myocardial infarction, unstable angina, severe arrhythmia, and considering the prohibition to use nicotine replacement therapy) [29], not being pregnant or breastfeeding, residing in Bandar Abbas, and giving consent to participate in the study are among the inclusion criteria.

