#### Ethical consideration

Ethical approval was received for this study from the National Institute for Medical Research Development Grant No. 983514. The trial was registered in the Iranian Trial Registry (IRCT20190126042494N1).

To introduce the researcher to the study environment; a formal letter will be obtained from the university’s research deputy. In the qualitative section, before conducting the interviews, appropriate relationship will be established by the interviewee (introducing the researcher, educational degree, aims of the study, and the reason for selecting the interviewee). Then, A written consent will be obtained from the participants for audio recording. They will be also assured about the confidentiality of their information. In the intervention section and prior to the sampling, the researcher will submit the formal letter, and then introduce herself and explain the aims of study to the women in target group in a clear manner. Then, a written consent will be obtained from the participants and emphasis will be made on the voluntarily participation in the study. Participants will also be assured that their information will remain confidential with the researcher.

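### Centres are assigned to arms before women are screened and consented, with no concealment described, so the arms can differ at entry through eligibility judgement and refusal

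*Protocol article*

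**What the plan says.** The Recruitment section under Step 6 gives the steps in order.

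- Centres come first: "First, four comprehensive health centers will be randomly selected in Bandar Abbas".
- Arms follow at once: "from which, two will be randomly assigned to the intervention group and two to the control group".
- A study investigator then draws one family record at random from the population of the selected centres. After that, "the researcher will visit all houses on the right side of the first selected record".
- Consent comes last: "After identifying the samples and obtaining informed consent from them", telephone numbers are collected.

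Inclusion criteria makes agreement a condition of entry: "giving consent to participate in the study are among the inclusion criteria". The other criteria include hookah use four times a week over at least six months, and psychiatric and cardiovascular history. Ethical consideration says that, before consent, the researcher will "introduce herself and explain the aims of study to the women in target group in a clear manner".

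Exclusion criteria places a pretest before the intervention begins. Duration of the intervention gives three months for recruiting and training the women, followed by 12 months of follow-up.

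**The concern.** When whole centres are allocated, every woman in a centre shares its arm. Randomising centres protects the comparison of women only if entry to the sample does not depend on the arm. If women are screened and consented after the draw, by someone who may know its result, two routes are open:

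- **Eligibility.** A borderline account of smoking frequency or medical history may be read differently in the two arms.
- **Consent.** Women may accept or refuse at different rates, or for different reasons, depending on what they are told or sense about what follows.

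Either route can give arms that differ in readiness to quit before any training. The primary outcome is cessation, and the limitations section says that it will not be biochemically validated, so a difference in motivation at entry bears directly on the main comparison. The article's own Background calls low participation a main challenge and puts mean adult participation in intervention programmes at about 2%. That figure is general and not a forecast for this trial, but it shows that the authors regard participation as selective.

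**Working it through.** **Step 1. Order of events.** The text runs: select centres, assign arms, draw a record, visit houses, identify women, obtain consent. Nothing places identification or consent before the assignment.

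**Step 2. Does the recruiter know the arm?** The article does not say so. The inference rests on three facts: assignment comes first, all women of a centre share one arm, and no masking of the recruiter is described. The recruiting and explaining are done by study investigators, not by independent staff. The inference is strong but remains an inference.

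**Step 3. What the existing safeguards cover.**

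| Stage | Safeguard in the text | Protected from knowledge of the arm? |
|---|---|---|
| Starting household | Random family record | Yes, in large part |
| Next households | All houses on one side | Yes, in large part |
| Eligibility | None described | No |
| Consent | None described | No |
| After entry | Pretest before the intervention | Measured differences can be seen and adjusted for |

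**Step 4. The plan's own figure, for scale.** The Sample size section gives d = 1, SDs 2.55 and 2.38, α = 0.05 and power 80%. Taking α as two-sided:

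n = (2.55² + 2.38²) × (1.960 + 0.842)² / 1² = 12.167 × 7.849 = 95.5, rounded up to 96 per group. This reproduces the stated 96. For 10% dropout, 96 × 1.1 = 105.6 gives the stated 106 (96 / 0.9 = 106.7 would give 107).

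**Step 5. Illustration with assumed shifts.** These shifts are not in the documents. The common SD is √[(2.55² + 2.38²)/2] = 2.466, and SE = 2.466 × √(2/96) = 0.356. With no training effect but an entry difference of b points on the self-efficacy scale used for sample size, and ignoring clustering, the false-positive rate is

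1 − Φ(1.96 − b/SE) + Φ(−1.96 − b/SE).

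| Assumed b (points) | False-positive rate |
|---|---|
| 0 | 5.0% |
| 0.10 | 5.9% |
| 0.25 | 10.8% |
| 0.50 | 29.0% |
| 0.75 | 55.8% |

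A larger sample does not help: b stays the same while SE shrinks.

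**Step 6. The same idea on cessation, also assumed.** If women ready to quit stop at 25% and others at 5%, an excess of 10 to 20 percentage points of ready women in one arm gives (0.25 − 0.05) × 0.10 = 0.02 to (0.25 − 0.05) × 0.20 = 0.04, a spurious 2 to 4 points. For comparison, with 96 per group and assumed quit rates of 10% to 15%, the SE of a difference is √(2 × 0.10 × 0.90/96) = 4.3 points to √(2 × 0.15 × 0.85/96) = 5.2 points, again ignoring clustering. On these assumptions the bias is below one standard error.

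**The case against.** The other side has several sound points.

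- **Knowledge of the arm is not stated.** A reader might take it as fact that the recruiter knows the arm at every door. The article never says this, and the passage under Ethical consideration shows only that the researcher explains the aims.
- **Different requests in the two arms are not stated.** A reader might suppose that intervention women are asked to join a course and controls only to answer questionnaires. The article describes one explanation for all women and says that the activities are presented to the intervention sample later, which suggests they are already enrolled. What controls are told is not described, and a condensed article may leave consent wording to the full protocol.
- **Household selection is constrained.** The random start and the all-houses rule narrow the problem to eligibility and refusal.
- **The pretest helps.** A reader might conclude that any imbalance could not be told apart from a training effect. That goes too far: measured differences can be seen, and logistic regression is among the listed methods.
- **Two centres per arm do not bar adjustment.** Readiness to quit belongs to individual women and could be measured on about 212 of them (2 × 106). The limit is unmeasured differences. The small number of centres is a different problem.
- **The design is labelled quasi-experimental**, so full protection by randomisation is not claimed.

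These points narrow the concern without removing it. The point challenges an order that the article states and does not depend on a missing detail. A common consent text would still leave eligibility to someone who may know the arm. The quasi-experimental label does not change the fact that the centres are randomised and that this order gives away part of the benefit.

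**Conclusion.** The concern holds in a limited form. As written, assignment precedes identification, screening and consent, and no concealment is described, so the arms **can** differ at entry through differential eligibility judgement or refusal. The text does not show that they **will** differ.

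The conclusion rests on the stated order, which is explicit, and on the recruiter probably knowing the arm, which is inferred. It does not need a different request to each arm. Adjustment for the pretest would deal with measured differences only.

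The size is unknown. The illustrations run from negligible (5.9% false positives for a 0.10-point shift) to serious (29.0% for 0.50 points), and every shift is assumed. The self-efficacy figures also concern the sample-size variable and not the primary outcome of cessation. None of them should be cited as an estimate of bias in this trial. The change is worth making because it is cheap and can be made before recruitment begins.

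**What to change.** Reorder the Recruitment section:

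1. Select the four centres at random, as now.
2. In all four, draw the starting record, visit houses, screen, consent and pretest the women, using one common information sheet and one screening log.
3. Only when enrolment is complete in all four, draw the two centres that receive the training.
4. Report the numbers approached, eligible and consented by centre and arm, so that any remaining selection is visible.

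If the draw cannot be delayed, a weaker alternative is a recruiter kept unaware of each centre's arm, with the same consent text everywhere.

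**Cost.** The steps already exist and no staff are added. Training cannot start in any centre until enrolment has finished in all four, and women enrolled early will wait longer between pretest and training. The three months given under Duration of the intervention for recruitment and training may therefore need to be restated.

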## Background

Today, the use of hookahs is considered as one of the most important global issues, especially in Arab countries, Turkey, and Iran [1]. Eastern Mediterranean region have the highest prevalence rate of hookah smoking (HS), and this trend has been increasing in the last two decades [2–4].

Social, psychological, cultural, and biological differences between women and men, especially in relation to causes of tendency towards various substances, have made it more obvious that this issue is more acute among women compared to men [5]. Based on women’s perception, social acceptance is higher for hookah than for cigarette [6]; and women have a more positive attitude toward hookah compared to men [7]. Accordingly, the world-wide statistics indicate an increase in the rate of hookah consumption among women compared to men [8, 9].

In Iran, women have more restrictions on the use of cigarettes than hookahs [10]. The results of a widespread survey performed in 2007 showed that 82% of Iranian women prefer smoking hookah than cigarette, and this makes hookah the most popular means of smoking compared to the other ones (pipe, cigarettes, etc.) [11].

In an epidemiological survey, the prevalence of hookah consumption among women in three southern provinces of Iran was estimated to be 16.8% in Sistan, 14.8% in Bushehr, and 10.3% in Hormozgan [12]. This rate is 7% to 8% among women in Eastern Mediterranean region [13], 4% among Lebanese women [14], and 4% among Pakistani women [15].

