### Step 6: Planning the evaluation

Evaluating each one of the intended health outcomes, behavioral and environmental determinants, and change objectives of HS will be addressed by designing evaluation questions and taking into account the budget and time frame. In this step, we will review the logical pattern of change and design evaluation questions based on determinants, behavioral and environmental goals, change objectives, and outcomes. We will then evaluate the effectiveness of designed program in a quasi-experimental study. The purpose of quasi-experimental intervention will be evaluating the effectiveness of designed educational intervention on smoking cessation/reduction rate among women.

The target population in this study will be all 15 years old women and older in Bandar Abbas.

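### Within each centre only the starting family record is random; the other women come from the adjoining houses, so each centre contributes one neighbourhood block and each arm about two

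*Protocol article*

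**What the plan says.** All of this is in the protocol article, Step 6, mostly under Recruitment.

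- The sampling is labelled as random without qualification: "The random method will be used for sampling".
- Four comprehensive health centres are drawn at random, of which "two will be randomly assigned to the intervention group and two to the control group".
- Each centre has a quota: "The number of samples from each center will be determined according to the population covered by the center".
- Within that frame, "SD will randomly select a family record belonging to the population covered by the selected comprehensive health centers". The record is in the singular.
- For the remaining women, "the researcher will visit all houses on the right side of the first selected record".

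No further random draw, sampling interval or limit on the length of the run is given. The opening of Step 6 defines the population of interest: "The target population in this study will be all 15 years old women and older in Bandar Abbas". The residence requirement under Inclusion criteria is to live in the city: "residing in Bandar Abbas, and giving consent to participate in the study are among the inclusion criteria".

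**The concern.** The label and the procedure do not match. Randomness operates when centres are chosen and allocated, and once more when the starting record is drawn. After that, who enters the trial is decided by who lives next along the street.

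This matters for this behaviour in particular. In Step 2, Determining the aims of intervention, the protocol's own example of a cause of hookah smoking is time spent with friends who smoke, and it plans one of its two matrices at the interpersonal level. Neighbouring women are therefore likely to resemble one another in smoking pattern, attitudes and readiness to quit, and to influence one another during follow-up. There are two consequences.

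- One block carries less information about the women a centre serves than the same number of women spread over its register.
- With about two blocks per arm, a baseline or outcome difference can arise from the choice of starting point. Random allocation of four centres gives little protection against that.

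No later analysis can restore a spread that was not sampled, so the change has to come before recruitment.

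**Working it through.** **1. The plan's own figure.** Under Sample size, d = 1, s1 = 2.55, s2 = 2.38, α = 0.05 (two-sided assumed) and power is 80%.

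n per group = (s1² + s2²)(z₀.₉₇₅ + z₀.₈₀)² / d² = (6.5025 + 5.6644) × 7.849 / 1 = 95.5, rounded up to 96.

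With 10% loss, 96 × 1.10 = 105.6, so 106, as stated (dividing by 0.90 gives 107). The figure reproduces. The formula treats the women as independent.

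**2. Women per block.** 2 × 106 = 212 women; 212 / 4 = 53 per centre. Equal quotas are an assumption, because the protocol makes quotas proportional to population covered.

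**3. Number of blocks.** The text says a single record and sets quotas by centre. The natural reading is one starting record per centre, so four blocks, two per arm. The words per centre do not appear. A literal reading of one record overall would be worse and could not fill four quotas.

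**4. Length of a run (illustrative only).** Background gives the prevalence of hookah use among women as "16.8% in Sistan, 14.8% in Bushehr, and 10.3% in Hormozgan"; Bandar Abbas is taken here under the Hormozgan figure.

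- At 10.3%: 53 / 0.103 ≈ 515 women aged 15 or older to screen. With an assumed 2 to 1 such women per house, that is about 258 to 515 consecutive houses per start.
- At 16.8%, taken as an upper alternative: 53 / 0.168 ≈ 316 women, so about 158 to 316 houses.

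These counts treat every smoker as eligible and come before refusals and exclusions. They show only that a block would be a sizeable stretch of one neighbourhood.

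**5. What spreading the starts would change.** Let ρ be the correlation between women in the same run of houses. The documents give no value, so a range is shown. The design effect is 1 + (m − 1)ρ, with m women per run. One run gives m = 53; ten runs give m = 53 / 10 = 5.3. Effective number per arm = 106 / design effect.

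| ρ (assumed) | One run of 53: design effect | Effective n per arm | Ten runs of 5.3: design effect | Effective n per arm |
|---|---|---|---|---|
| 0.01 | 1 + 52 × 0.01 = 1.52 | 69.7 | 1 + 4.3 × 0.01 = 1.04 | 101.6 |
| 0.02 | 1 + 52 × 0.02 = 2.04 | 52.0 | 1 + 4.3 × 0.02 = 1.09 | 97.6 |
| 0.05 | 1 + 52 × 0.05 = 3.60 | 29.4 | 1 + 4.3 × 0.05 = 1.22 | 87.2 |

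The table isolates similarity among neighbours. Differences between whole centres come on top of it, and more starting points do not reduce them.

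**The case against.** The strongest reply is that this is a quasi-experimental comparison of arms and not a prevalence survey. Centres are chosen and allocated at random, the target population is named without any claim that the sample represents it statistically, and a comparison between arms does not need a simple random sample within centres. That is fair as far as it goes. It does not answer the point that about two blocks per arm make the comparison itself depend on the starting points, nor that the label overstates what is done.

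A reader might also infer more than the text supports.

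- **That the run of houses will leave the centre's catchment.** No catchment sizes are given, so house counts cannot show this. The per-centre quotas, and a starting record tied to the covered population, suggest an intent to stay inside.
- **That women living across a boundary contaminate the arms.** Step 6 (text under Exclusion criteria) directs the training at women enrolled in the intervention group, not at everyone registered with a centre. A woman is not exposed, or deprived of exposure, merely by where her house lies.
- **That eligibility is left open, or that several women per house will be enrolled.** The inclusion list is worded as partial, and boundary and household rules are field detail that a condensed article may leave out. Silence is not a stated rule.

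A fully random list of houses would also be a heavy remedy. Nothing says the family records hold hookah status, so hundreds of scattered houses per centre might have to be visited. That objection stands, and the fix below avoids it.

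**Conclusion.** The point holds in a limited form. As written, the within-centre procedure is one random start followed by consecutive houses, and nothing elsewhere in the article alters it. Each centre's sample is then one neighbourhood block, with about two blocks per arm, and the unqualified description as random does not fit.

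The size cannot be fixed from the documents. With an assumed neighbour correlation of 0.01 to 0.05 and equal quotas, the design effect from a single block is 1.52 to 3.60, against 1.04 to 1.22 with ten starts. The conclusion rests on the per-centre reading of the single record and on neighbours being alike, which the protocol's account of hookah smoking as social makes likely but does not measure. It does not rest on any run crossing a catchment boundary or on contamination between arms; neither can be shown. The change should be made before recruitment, but it does not by itself invalidate the trial.

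**What to change.** In Recruitment, replace the single start with several. From each selected centre's register of family records, draw a number of random starting records (for example 10 or more), and visit a short run of houses from each until the centre's quota is met. State in the same place that only women covered by that centre are enrolled and that a woman's arm is the arm of that centre. Describe the method as what it is: random selection and allocation of centres, random starting records within centres, and short runs of neighbouring houses.

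The cost is more travel and field time. The register is already used for the first draw, and sample size and staff are unchanged. The change reduces dependence on a single neighbourhood within each centre. It leaves the limit of two centres per arm as it is, and the report should acknowledge that limit separately.

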#### Inclusion criteria

Smoking hookah for 4 times a week in a duration of at least 6 months before the data collection [27, 28], being fluent in native language, having no history of psychiatric disorder, cardiovascular disease (acute myocardial infarction, unstable angina, severe arrhythmia, and considering the prohibition to use nicotine replacement therapy) [29], not being pregnant or breastfeeding, residing in Bandar Abbas, and giving consent to participate in the study are among the inclusion criteria.

#### Exclusion criteria

Simultaneous use of cigarettes and other tobacco products or drugs, and being absent in more than 20% of the training sessions are among the exclusion criteria.

With regard to the research objectives set out in the previous steps, appropriate training strategies and activities will be selected for the intervention group, and later on, the types of anticipated activities will be introduced to the samples in intervention group in terms of the scheduled program. Then, the training intervention will be implemented based on the previous steps. The number of sessions, duration of each session and intervention, and number of participant in each intervention session will be determined by the research team according to the needs of intervention group. The assessment will be performed based on a pretest that will be taken before the beginning of the intervention, as well as 3، 6, and 12 months after the start of training program.

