Considering the complexity of behaviors such as smoking; different models and theories have been developed in health education, which in the situation of appropriately applying, they could result in reducing the rate of harmful behaviors [16]. In smoking cessation interventions, relevant and effective techniques of behavioral change should be used [17]. The designers’ goal will be producing a product from an intervention, which is complex and requires a set of behavioral change techniques. Thus, program designers should be able to present numerous theoretical-practical approaches [17]. On the other hand, one of the main challenges of smoking cessation is the lack of participation of target group in the interventions. Among adults, the mean ratio of participation in intervention programs is approximately 2%. [18]. Therefore, to stop hookah smoking, it seems that several factors such as the use of coherent, ecological, and theoretical-based approach as a roadmap to provide guidelines for designing evidence-based interventions, using relevant and effective techniques of behavioral change, and participation of target population are essential.

Intervention mapping (IM) introduces a series of systematic steps and processes that help health promoters to develop theoretical and evidence-based programs. IM is characterized by three factors as follows: ecological approach, participation of all stakeholders, and the use of theory and evidence. IM describes the process of planning health promotion programs in six steps as follows: (1) assessing the needs; (2) creating the matrix of goals for behavioral change; (3) choosing theory-based approaches and practical strategies; (4) developing the intervention; (5) planning the implementation of program; and (6) planning the evaluation [19].

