#### Quality control of the intervention development process

At this stage, the researcher will invite the participants to obtain their views on the components and materials of the program; and based on their views and cultural issues, the materials and components of the program will be revised. At first, five training sessions will be held on theoretical approaches and practical applications for women and those who have influence on them. Each session is estimated to take 90 min and will be held once a week. Materials and components of the program will be reviewed.

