#### Sample size

To calculate the sample size in this semi-experimental study, the sampling formula in comparative studies will be used, considering (d = 1, s1 = 2.55 and s2 = 2.38, respectively) based on the findings of similar studies (self-efficacy three months after training in both intervention and control groups in the study of Ahmed Sotoudeh), [26]. Also, considering the errors of α = 0.05 and β = 0.2 (power of 80%), the sample size will be calculated as 96 individuals in each group. However, by taking 10% sample drop into account, the number of samples in each group will be estimated as 106 individuals.

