#### Instrument

The measurement tool will be similar to the final version of questionnaire, which will be designed based on the matrix (change, determinants, and practical objectives). The questionnaire will consist of two parts as follows: demographic information, and change objectives and expected outcomes of the program. The validity and reliability of the questions will be examined by the opinions of a number of experienced experts in this field.

*The measurement of primary outcomes* (1) level of hookah cessation immediately after the intervention, (2) level of hookah cessation within 3 months of the intervention, (3) level of hookah cessation within 6 months of the intervention, and (4) level of hookah cessation within 9 months of the intervention.

*The measurement of secondary outcomes* (1) Comparison of the frequency of hookah consumption before and after the intervention for those who did not stop hookah smoking, (2) point prevalence of study participants (no hookah use during the past 7 days) at the end of the intervention and at 3, 6 and 12 month follow-up, (3) comparison of the number of hookah cessation attempts before and after the intervention, (4) participants’ tendency to stop hookah 6 months after the intervention, (5) rate of cessation as a result of intervention among the study participants after 6 months, and (6) rate of cessation as a result of intervention among the study participants after 12 months.

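### The attendance-based exclusion acts after allocation and can remove women from the intervention arm only, so it can bias the cessation comparison

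*Protocol article*

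**What the plan says.** The sequence comes from four sections of the protocol article.

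- **Recruitment.** Four health centres are drawn at random, of which "two will be randomly assigned to the intervention group and two to the control group". Women are then found within the centres and asked for consent, and their phone numbers are taken.
- **Exclusion criteria.** Alongside use of other tobacco products or drugs, the section says: "being absent in more than 20% of the training sessions are among the exclusion criteria". It then says that "appropriate training strategies and activities will be selected for the intervention group". The number and length of sessions "will be determined by the research team according to the needs of intervention group". No sessions are described for control women.
- **Instrument.** The primary outcomes are levels of cessation at several times, the first being "level of hookah cessation immediately after the intervention".
- **Planning the evaluation (Step 6).** The purpose is to evaluate how effective the programme is for cessation or reduction among women. The target population is all women aged 15 and over in the city.

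The Statistical analysis section lists t-tests, path analysis and logistic regression. Neither it nor any other section says that women excluded for absence stay in follow-up or are analysed as allocated.

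**The concern.** An eligibility criterion should be decidable before allocation. This one is decided by behaviour after allocation, and only where there are sessions to miss. Applied as written, it compares the better-attending part of the intervention arm with the whole control arm. Control women who would have missed sessions had they been offered them cannot be identified, so they all stay in.

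Motivation to quit may well drive both attendance and quitting. If so, a programme with no effect would still show a higher cessation rate in its arm. The result would describe women who attend, while the stated aim is effectiveness among women in general.

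If exclusion also ends follow-up, the outcomes of these women are never collected and no later analysis can restore them.

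**Working it through.** **1. Is the rule post-allocation and one-armed?** Reading the sections in order gives: centres allocated, women identified and consented, training given to the intervention group, attendance counted. The rule acts at the last step, in the only arm with sessions. This needs no arithmetic.

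**2. Can the share removed be derived?** No. The number of trial sessions is left open, and the trigger depends on it:

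- 4 sessions: one absence is 1/4 = 25%, so one absence excludes.
- 5 sessions: one absence is 1/5 = 20%, which is allowed; two are 40%, so two exclude.
- 10 sessions: two absences are 20%, which is allowed; three exclude.

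**3. Illustrative shares removed.** Assumptions, none from the documents: five sessions, and attendance independent between sessions with probability q each.

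Share removed f = P(at least 2 of 5 missed) = 1 − q⁵ − 5(1 − q)q⁴

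- q = 0.90: 1 − 0.5905 − 0.3281 = 0.081
- q = 0.85: 1 − 0.4437 − 0.3915 = 0.165
- q = 0.80: 1 − 0.3277 − 0.4096 = 0.263

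Missed sessions probably cluster within women, so these shares only set a scale.

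**4. Illustrative bias with no true effect.** Assumptions: a 15% quit rate in both full arms, and women kept by the rule three times as likely to quit as those removed. Let l be the quit rate among those removed. Then 0.15 = f·l + (1 − f)·3l, so the rate among women kept is 3l = 0.45 / [f + 3(1 − f)].

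| f | Rate among women kept | Control | Spurious gain |
|---|---|---|---|
| 0.081 | 0.45/2.838 = 15.9% | 15% | +0.9 points |
| 0.165 | 0.45/2.670 = 16.9% | 15% | +1.9 points |
| 0.263 | 0.45/2.474 = 18.2% | 15% | +3.2 points |

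**5. Dependence on the assumed gradient.** If the ratio is 1 instead of 3, the rate among women kept is 15% and the bias is zero for every f. Put another way, at f = 0.20, if removed women quit at half the overall rate, the rate among women kept is (0.15 − 0.20 × 0.075)/0.80 = 16.9%, or +1.9 points. If none of them quits, it is 0.15/0.80 = 18.75%, or about +3.8 points, the most possible at that share and quit rate.

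**6. The plan's own sample size.** The stated inputs reproduce it: (1.960 + 0.842)² × (2.55² + 2.38²)/1² = 95.5, so 96 per group; 96 × 1.10 = 105.6, so 106. That calculation concerns a difference in mean self-efficacy, and this point does not rest on it.

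**The case against.** The best defence is that analysis sets belong in an analysis plan, which may exist unseen and may specify analysis as allocated. That would answer a complaint about a missing definition. Here, though, the article itself states a rule that removes women, and an analysis plan cannot supply outcomes that were not collected. One might also note that Duration of the intervention speaks of the women being trained without naming an arm. The Exclusion criteria section, however, ties training activities to the intervention group, and no control sessions appear anywhere.

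Several stronger readings are tempting but not supported:

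- **That the bias certainly favours the programme.** The documents give no link between attendance and quitting. The direction is an assumption.
- **That the trial has five sessions.** The sentence "At first, five training sessions will be held on theoretical approaches and practical applications" belongs to quality control of intervention development (Step 4), where materials are reviewed with women and those who influence them. It does not set the trial programme; five is used above only as an example.
- **That the rule discards the very failures the Background warns of.** The Background does say that "one of the main challenges of smoking cessation is the lack of participation of target group in the interventions", but it follows this with a mean participation of about 2% among adults. That reads as uptake of programmes, not as sessions missed by women who have consented.
- **That the rule overruns the dropout allowance and so costs a known amount of power.** The allowance, made "by taking 10% sample drop into account", is attached to a self-efficacy calculation. Exceeding it does not measure lost power for cessation.
- **That full comparability is destroyed.** With two centres per arm and women identified after allocation, individual comparability is already limited. The rule makes a weak balance weaker.

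**Conclusion.** The defect stands: the protocol fixes an exclusion that operates after allocation, can apply in one arm only, and comes with no statement that the excluded women are followed or analysed. This follows from the text alone.

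The consequence is conditional. If poor attenders quit less often, intervention-arm cessation is overstated; if they quit as often as attenders, there is no bias. Under the assumed 15% quit rate, threefold ratio and 8% to 26% removed, the false gain is about 1 to 3 percentage points. This is an illustration and not an estimate, because the documents fix neither the number of sessions nor any attendance or quit rate. The rule should be changed before recruitment, since follow-up that is not done cannot be recovered.

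**What to change.** Delete attendance from the exclusion criteria. State that every consented woman is followed to the last assessment and analysed in the arm of her centre, whatever her attendance. Record attendance as a process measure. If the effect in attenders is of interest, compare women attending at least 80% of sessions with controls in a secondary analysis labelled per-protocol, and fix the number of sessions beforehand so that the threshold has a denominator.

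The cost is a change of wording and follow-up questionnaires for non-attenders, which is feasible because phone numbers are collected from all participants. The effect estimate may come out somewhat smaller.
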